## Abstract

**Background:**

Patients undergoing surgery for esophageal cancer have a high risk for postoperative deterioration of lung function and pulmonary complications. This is partly due to one-lung ventilation during thoracotomy. This often accounts for prolonged stay on intensive care units, delayed postoperative reconvalescence and reduced quality of life. Socioeconomic disadvantages can result from these problems. Physical preconditioning has become a crucial leverage to optimize fitness and lung function in patients scheduled for esophagectomy, in particular during the time period of neoadjuvant therapy.

**Methods/Study design:**

We designed a prospective multicenter randomized-controlled trial. The objective is to evaluate the impact of an internet-based exercise program on postoperative respiratory parameters and pneumonia rates in patients with Barrett’s carcinoma scheduled for esophagectomy. Patients are randomly assigned to either execute internet-based perioperative exercise program (iPEP), including daily endurance, resistance and ventilation training or treatment as usual (TAU). During neoadjuvant therapy and recovery, patients in the intervention group receive an individually designed intensive exercise program based on functional measurements at baseline. Personal feedback of the supervisor with customized training programs is provided in weekly intervals.

**Discussion:**

This study will evaluate if an intensive individually adapted training program via online supervision during neoadjuvant therapy will improve cardiorespiratory fitness and reduce pulmonary complications following esophagectomy for Barrett’s cancer.

**Trial registration:**

NCT02478996, registered 26 May 2015.

## Background

Risk management in esophageal surgery has become an essential feature with regard to postoperative outcome [1]. Although perioperative mortality in esophageal cancer surgery could be steadily reduced in recent years, morbidity is still high, and affects 30–50% of patients – even in the current literature and large surgical centers [2]. Pulmonary complications following esophagectomy are the most common and cost-intensive adverse events, mostly due to prolonged intensive care unit stays. This is partly due to one-lung ventilation (OLV) during thoracotomy. During OLV, the operated lung remains completely atelectatic. The non-ventilated lung is known to be hypoperfused owing to hypoxic vasoconstriction, and when the bronchial block is ended, the ensuing immediate lung re-expansion along with tissue reperfusion generates oxygen-derived free radicals. The single-ventilated lung is subjected to a combination of hyperoxia, volutrauma, and hyperinflation. Esophageal complications are not only life-threatening and associated with a high mortality in the short-term postoperative course, but have also exerted a long-lasting negative effect on Health-Related Quality of Life (HRQL) in patients who survive 5 years after esophagectomy for cancer [3]. Advances in surgical techniques, such as minimally-invasive esophagectomy (MIE), have been proposed to reduce surgical risk and perioperative morbidity and mortality, thus improving surgical short- and long-term outcomes. However, to the best of our knowledge, there is only one fully published prospective randomized trial comparing minimally-invasive versus conventional / open surgery (“time trial” = “**t**raditional **i**nvasive vs. **m**inimally-invasive **e**sophagectomy”) [4]. In this study, a significantly reduced rate of pulmonary infections in patients receiving minimally-invasive treatment versus open surgery was reported [4]. This striking result after 2 weeks following surgery might be due to the reduced trauma of thoracoscopy compared to thoracotomy. In addition, oncologic parameters, such as clear resection margins, and the number of dissected lymph nodes, were comparable in both groups [4]. As impressively shown for colorectal surgery, “fast-track” (FT) rehabilitation or enhanced recovery after surgery (ERAS) programs in visceral surgery, comprising atraumatic surgical techniques, stress-reduction of the organism as a response to major surgery, and a decrease of postoperative organ dysfunction, leads to fewer perioperative complications, while reducing hospital costs and increasing patient turnover by shorter lengths of in-hospital stay [5, 6]. However, there are only few studies with limited case numbers regarding fast-track concepts in esophageal surgery [7–12]. Although no routine use of minimally-invasive surgery and other advances of modern surgical techniques were applied, all studies revealed a very short ICU stay, early extubation, thoracic peridural anaesthesia, multimodal pain management, early enteral nutrition (usually via a jejunal catheter), enhanced postoperative mobilisation, and physio−/ ventilation therapy [7–12]. Fast-tracking or enhanced recovery programs for esophagectomy are promising, but still far from reaching the results of e.g. colorectal or minor non-oncological surgery, owing to the higher invasiveness of the procedure with the associated increased general and surgical risk.

A recently published systematic review concluded that preoperative exercise therapy can be effective for reducing postoperative complication rates and lengths of hospital stay after cardiac and abdominal surgery [13]. Preoperative physical activities were lower in patients who developed postoperative pulmonary complications in a study by Feeney et al. [14]. Taking into account the importance of the physical condition, the preoperative physical activity level should be further examined [14]. A prospective observational study by Tatematsu et al. confirmed low-level physical activity – among others – as a significant risk factor for postoperative complications after esophagectomy [15].

One randomized controlled pilot study [16], two non-randomized controlled pilot studies [17, 18], one retrospective cohort study [19], and one study protocol [20] are available in the current literature with regard to preoperative inspiratory muscle training and postoperative pulmonary complications in patients undergoing esophagectomy. In all studies, preoperative inspiratory muscle training was feasible and effective as it resulted in a reduced postoperative pulmonary complication rate [16–19]. Following these encouraging results, we designed an internet-based exercise program for patients scheduled for esophagectomy. The objective of this study is to investigate the pulmonary outcomes of physically preconditioned patients with Barrett’s cancer scheduled for esophagectomy who receive physical training during the phase of neoadjuvant therapy.

## Methods/Study design

This is a prospective multicenter randomized-controlled trial organized by the Department of Sports Medicine, Disease Prevention and Rehabilitation of the Johannes Gutenberg-University of Mainz, Germany, and the Department of Visceral, Transplant, Thoracic and Vascular Surgery of the University Medical Center of Leipzig, Germany. Patients are randomly assigned to either undergo internet-based perioperative exercise program (iPEP) (intervention group) or treatment as usual (TAU) (control group). The randomization procedure is performed using an online random number generator, which is provided by the University of Geneva’s online service [21]. Randomization is stratified by center. The study is funded by the “Barrett-Initiative e.V.” (http://www.barrett-initiative.de/). Inclusion (Table 1) and exclusion (Table 2) criteria are clearly defined. Primary staging, neoadjuvant treatment, preoperative nutrition as customized to the initial nutritional risk screening (NRS) [22], re-staging, preoperative peridural anesthesia, abdomino-thoracic esophagectomy with 2-field lymph node dissection and intrathoracic anastomosis, postoperative fluid management and nutrition, analgesia, physical therapy, mobilization and ventilation therapy following esophagectomy as well as rehabilitation are performed according to standard operating procedures (SOPs). At the beginning of the study, smokers are advised and supported to stop smoking by smoking cessation programs when needed. Smoking habits are recorded throughout the study.

**Table 1 Tab1:** Inclusion criteria

#	Inclusion criteria
1.	Histologically proven adenocarcinoma of the esophagus or adenocarcinoma of the esophagogastric junction type I-II according to Siewert’s classification, clinical stages IIB-IIIC (T3/T4 and/or N+; M0) according to UICC, 7th edition
2.	Male
3.	Age between 18 and 75 years
4.	Resectable stage according to discussion in the local multidisciplinary tumor board (MDT) of the participating centers and patient medically fit for multimodality therapy (ECOG performance status at least 1 or better, no severe impairment of cardiac, renal, hepatic, endocrine, bone marrow and cerebral functions)
5.	Planned abdomino-thoracic esophagectomy with gastric pull-up and intrathoracic or cervical anastomosis
6.	Cognitive ability of the patient to understand the perioperative program and to participate actively [40, 41]

**Table 2 Tab2:** Exclusion criteria

#	Exclusion criteria
1.	Presence of a second malignant tumor (unless curatively treated >5 years ago)
2.	Chemotherapy or radiochemotherapy in patient’s history
3.	Orthopedic, rheumatologic, cardiovascular or neurologic (epilepsy, stroke, Parkinson’s disease, muscle wasting diseases such as amyotrophic lateral sclerosis or multiple sclerosis) contraindications for the exercise program
4.	Inability to use the internet or no internet access
5.	Inability to communicate in German
6.	Each active disease, which hinders completion of the study
7.	Active alcoholism or illegal drug consumption within the last six months before study entry

Primary objective of the trial is to investigate the effect of the perioperative training on physical capacity.

Primary endpoint is the change in peak oxygen uptake (VO_2peak_) prior to surgery as compared to baseline.

Secondary endpoints areChange in VO_2peak_ at 12 weeks after surgeryChange in Forced Expiratory Volume in 1 s (FEV1) directly prior to surgery and at 12 weeks after surgeryChange in Forced Vital Capacity (FVC) directly prior to surgery and at 12 weeks after surgery

All respiratory parameters are assessed by a spirometer.

Further secondary endpoints encompass pneumonia within 12 weeks after surgery, anastomotic insufficiency within 12 weeks after surgery (according to Veeramootoo et al.) [23], duration of mechanical ventilation, re-intubation rate, length of intensive care unit stay, postoperative in-hospital stay, feasibility of the internet-based exercise program, quality of life as assessed with the EORTC (European Organization for Research and Treatment of Cancer), QoLQ-C30 questionnaire with the esophagus-specific module OES-18 [24], and social support of disease coping by means of the modified *Berlin Social Support Scal*e [25].

### Sample-size calculation and statistical analyzes

Our assumptions for sample size calculation are based on reports investigating the effect of different training modalities on respiratory parameters in cancer patients during or after therapy [26–31]. We aim at detecting a difference in mean VO_2peak_ of 6 ml/min/kg between the two groups. This difference seems to be achievable, given the reports mentioned above. The reported standard deviation (SD) VO_2peak_ ranges between 2.3 and 10.7 ml/min/kg. For our trial, we rather conservatively assume a SD of 8 ml/min/kg. With these assumptions, a total of 58 patients (29 interventions and 29 controls) have to be analyzed to achieve a power of 80% at a significance level of 5% (two-group t-test). Because the primary endpoint is assessed by spiroergometry and this may be burdensome for patients, we estimate a rather high dropout-rate of about 30%. Taking this into account, a total of 80 participants (40 interventions and 40 controls) will be randomized.

Primary efficacy analysis will be performed by ANCOVA with baseline values of VO_2peak_ as covariates, thus increasing power. Confirmatory analysis will be based on all patients with available post-baseline VO_2peak_ measurement. Patients will be analyzed as randomized.

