## Discussion

In spite of significant advances in surgical techniques, postoperative intensive care and complication management, esophagectomy is still a high risk-procedure associated with considerable postoperative pulmonary morbidity and mortality. This often encounters for prolonged periods of reconvalescence and reduced quality of life, apart from socioeconomic disadvantages. In addition, postoperative pulmonary complications after esophagectomy are associated not only with worse short-, but also long-term outcomes [35]. Although morbidity and functional results following esophagectomy are known to be multifactorial, regular, structured physical activity and ventilation training before surgery seem to be the most relevant leverages to optimize results [13–20]. As most patients with locally advanced, potentially resectable esophageal cancer undergo neoadjuvant treatment, this period offers the possibility for improving fitness, even in patients with no or only few previous physical activities. As shown by a recent metaanalysis, neither neoadjuvant chemotherapy nor radiochemotherapy for esophageal carcinoma increases the risk of postoperative morbidity or perioperative mortality compared with surgery alone [36]. There was also no clear difference between the two neoadjuvant treatment modalities with respect to postoperative morbidity [36]. Therefore, both modalities are allowed in our study. The “*Nutrition and Physical Activity Guidelines for Cancer Survivors*” recommend a minimum of 150-min exercise per week, and strength training at least 2 days per week [37]. Because of the short intervention time and in order to achieve an optimum development of physical resources until surgery, a daily training is advised in our study. Participants should perform up to four units of endurance and up to 3 units of resistance training per week (approximately one hour per unit) in the last phase of training [38]. In addition, daily ventilation exercises are carried out with the “*Voldyne*” device [39].

To our knowledge, this is the first prospective randomized controlled trial to assess an internet-based perioperative setting for patients scheduled for esophagectomy.

To ensure individual extensive care, the use of our online exercise program is easily accessible.

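### Randomisation is stratified by centre, but the stated primary ANCOVA does not name centre; adding it is a cheap, minor gain in efficiency

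*Protocol article*

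**What the plan says.** Methods/Study design in the protocol article opens with "This is a prospective multicenter randomized-controlled trial" and later adds "Randomization is stratified by center". No other stratification factor is given. Block size and number of centres are not stated.

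The same section defines the outcome: "Primary endpoint is the change in peak oxygen uptake", measured before surgery against baseline.

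Sample-size calculation and statistical analyzes then gives the model. "Primary efficacy analysis will be performed by ANCOVA with baseline values of" VO2peak "as covariates, thus increasing power". Centre appears in no analysis statement in the article. The sample size itself comes from an unadjusted two-group t-test, for a difference "of 6 ml/min/kg between the two groups" and with the statement "we rather conservatively assume a SD of 8 ml/min/kg". This gives 58 patients to be analysed and 80 to be randomised, to allow for about 30% dropout.

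**The concern.** Stratifying by centre, when it balances the arms within centres, removes between-centre variation from the treatment comparison. A model without a centre term still counts that variation as residual noise. The reported standard error then exceeds the true variability of the estimate: confidence intervals are a little too wide and the test rejects less often than 5% under the null.

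The article names a covariate and gives the gain in power as its reason. The same reasoning applies to centre, which is already recorded for every patient and already used in the allocation. What is at stake is efficiency in a trial of about 58 evaluable patients, not the validity of a positive result.

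**Working it through.** **1. The plan's own figure.** Inputs from the article: difference 6, SD 8, power 80%, significance level 5% (two-sided assumed, since sidedness is not stated). Standardised effect = 6/8 = 0.75. The two-sample t-test needs 28.9, hence 29 per arm or 58 in total, with power 80.1%. The stated 58 reproduces.

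**2. What the baseline covariate adds.** With baseline-outcome correlation r, the residual SD is 8 × √(1 − r²), and the effect becomes 0.75/√(1 − r²). At 29 per arm, power is 80.1% for r = 0, 83.7% for r = 0.3 and 90.0% for r = 0.5. The article does not give r; these values are assumed.

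**3. Mechanism.** Let centre hold a share v of the variance left after baseline (assumed). For r = 0.5 the residual SD is 8 × √0.75 = 6.93, and the standard error with no centre effect is 2 × 6.93/√58 = 1.82. Under perfect within-centre balance, the true variability of the estimate shrinks by √(1 − v). At v = 0.20 that is 1.82 × √0.80 = 1.63. A model without centre misses most of this reduction.

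In closed form, type I error without centre is 2 × [1 − Φ(1.96/√(1 − v))]: 3.9% at v = 0.10 and 2.8% at v = 0.20. This is a limiting case. It needs perfect balance, and with few centres the realised between-centre variance is on average below its nominal share.

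**4. Simulation of the stated analysis.** 58 analysed, difference 6, SD 8, equal centres, blocks of four within centre unless marked, 6,000 runs per scenario. Number of centres, v, r and blocking are assumed. Residual variance after baseline is held fixed, so a larger v means less within-centre noise; this is why power rises down the table even without centre in the model.

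| Centres | v | r | Type I error, without / with centre (%) | Power, without / with centre (%) |
|---|---|---|---|---|
| 4 | 0 | 0.5 | 5.15 / 5.15 | 89.2 / 89.0 |
| 4 | 0.05 | 0.5 | 4.25 / 4.60 | 90.5 / 90.9 |
| 4 | 0.10 | 0.5 | 4.28 / 5.13 | 90.8 / 91.8 |
| 2 | 0.20 | 0.5 | 4.03 / 5.03 | 93.4 / 95.0 |
| 4 | 0.20 | 0.5 | 3.43 / 4.78 | 92.9 / 95.2 |
| 6 | 0.20 | 0.5 | 3.38 / 4.90 | 91.3 / 94.4 |
| 4 | 0.10 | 0 | 3.58 / 4.63 | 81.4 / 83.0 |
| 4 | 0.20 | 0 | 3.73 / 5.15 | 83.0 / 87.0 |
| 4, unblocked | 0.20 | 0.5 | 4.72 / 4.77 | 90.3 / 92.9 |

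Monte Carlo error is about √(0.05 × 0.95/6000) = 0.28 points for a type I error near 5%, so small differences should not be over-read. With four centres, v = 0.20 and r = 0.5 (blocked), the mean model standard error without centre is 1.79 against a true SD of 1.66. With centre it is 1.64 against 1.64.

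**5. Allowing for dropout.** A further simulation randomised 80 patients in four equal centres with blocks of four, and left 58 analysed after random dropout. Without centre, type I error was 3.3 to 3.5% at v = 0.20 and 4.6% at v = 0.05. Power without centre was 79.7 to 80.9% for r = 0 and 89 to 91% for r = 0.5. Adding centre gained about 0.5 to 2.5 points for v of 0.05 to 0.10 and 3.6 to 6 points at v = 0.20. At v = 0 it cost slightly.

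**6. Degrees of freedom.** With 58 analysed, the baseline-only model leaves 58 − 3 = 55. With four centres it leaves 58 − 6 = 52.

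**The case against.** The strongest reply is that leaving centre unnamed is not the same as excluding it. The text is a condensed article, the SAP is not shown, and the Discussion refers to a more detailed study protocol. The stratification sentence and the model sentence can both be true. This stands in part: there is no contradiction, and the full documents may already include centre. But the article does specify the primary model, its covariate and the reason for it, and as written that model omits the one stratification factor.

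Second, baseline VO2peak would absorb any stable difference between centres, so only a centre effect beyond baseline matters, and the article gives no figure for one. This stands. It makes the loss conditional, and a 20% share after baseline adjustment is a high assumption.

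Third, the clearly low type I errors require balance within centres. Blocking is not stated, and about 30% dropout with analysis of available cases disturbs balance. This also stands: without blocking, type I error was close to nominal, although adjustment still gained power.

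A reader might infer that centres test or treat patients differently and that neoadjuvant modality should also be a covariate. The documents do not support this. Methods/Study design says treatment follows standard operating procedures, and one treadmill protocol is given. The Discussion says "Therefore, both modalities are allowed in our study", which does not say that use varies by centre. Modality is not a stratification factor, so the argument from the design does not reach it.

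**Conclusion.** The point holds as a minor one. The only stratification factor is not named in the stated primary model. If centre holds 5 to 20% of residual variance, the test is conservative, with type I error roughly 3.3 to 4.7%. The power forgone is about 0 to 4 points, or up to about 6 at a 20% share with dropout. It is nil if centre has no effect beyond baseline. These figures rest on assumed centre numbers, shares, correlations and blocking, none of which the article gives.

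Two stronger readings are tempting and should not be drawn. One is that the result would be biased or falsely significant: the error runs in the conservative direction, so a positive result stands. The other is that the trial loses its planned power. The sample size comes from an unadjusted t-test, and the lowest simulated power without centre was 79.7%, at zero baseline correlation. What is forgone is mainly a possible gain above 80%.

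**What to change.** State the primary model as ANCOVA of pre-surgery VO2peak (or its change) on treatment, baseline VO2peak and centre. Fix before database lock either a rule for pooling very small centres or the use of a random centre effect; the Discussion invites further centres, so small ones may occur. If the full protocol or SAP already does this, confirming it settles the point.

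The cost is one line of wording and a few degrees of freedom out of about 56 (80 × 0.70 = 56 evaluable at exactly 30% dropout). If centre turns out to have no effect, the power loss is negligible: 89.2% against 89.0% with four centres.

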### Intervention

Before initial spiroergometry and echocardiography, participants will perform a breathing test, which provides information about actual inspiratory vital capacity. The patients perform a stepwise cardiopulmonary exercise test on a treadmill until exhaustion (Table 3). The test includes up to 14 stages and is increased by speed and angle of inclination. Termination of ergometry is indicated by meeting absolute or relative stop criteria (Table 4) [32].

**Table 3 Tab3:** Modified “walking protocol”

Stage	Speed (kilometers/hour)	Angle of inclination (degree)	Duration (minutes)
1	3	1.5	3
2	3.7	3.0	3
3	4.4	4.9	3
4	5.1	6.3	3
5	5.8	7.4	3
6	6.5	8.2	3
7	6.5	9.8	3
8	6.5	11.4	3
9	6.5	13.0	3
10	6.5	14.6	3
11	6.5	16.2	3
12	6.5	17.8	3
13	6.5	19.4	3
14	6.5	21.0	3

**Table 4 Tab4:** Absolute and relative criteria indicating termination of ergometry [31]

Absolute indication	Relative indication
ECG ST-segment depression ≥3 mm	Hypertensive dysregulation (RR_syst_ 230–260 mmHg, RR_diast_ ≥ 115 mmHg)
ECG ST-segment elevation ≥1 mm	Drop in blood pressure > 10 mmHg (compared to baseline blood pressure) without signs of myocardial ischemia (no angina pectoris, no ECG ST-segment depression)
Drop in blood pressure > 10 mmHg (compared to baseline blood pressure) with signs of myocardial ischemia (angina pectoris, ECG ST-segment depression)	Polymorphic extrasystols, duplets (2 consecutive ventricular extrasystols), salves (≥ 3 consecutive ventricular extrasystols)
Moderate-severe angina pectoris-symptoms	Supraventricular tachycardias
Severe dyspnea	Bradyarrhythmias
Clinical signs of less perfusion (cyanosis)	Line faults
Persistent (duration >30 s) ventricular tachycardias	Presence of line faults (high AV-blockage, branch block)
Exhaustion of the patient	reinforced angina pectoris symptoms
Technical problems (defect ECG-registration, monitor failure)	

